## Patients and samples

### Ethics approval and consent to participate

The CLEVER study has received approval from the Ethics Committee of Peking University People’s Hospital (approval number 2022PHB140-001). It is registered with ClinicalTrials. gov under the identifier NCT05352035. Patient recruitment for the study began in April 2022.

### Patients enrollment

#### Sample size calculation

The CLEVER study aims to recruit over 1000 patients to investigate the molecular evolution patterns of lung cancer in the Chinese population. It is anticipated that the proportion of recurrence events by the end of the follow-up period will range from 15% to 30%. We have calculated the sample size for the first phase of CLEVER through the following three considerations.

##### Consideration for survival analysis

In the first phase of the CLEVER study, we aim to compare 2-year DFS between predefined high-risk and low-risk groups using a two-sided log-rank test at α = 0.05 and 80% power (1-β = 0.80). Based on our preliminary data (CHN-P cohort),^[12]^ we assume a 2-year DFS event (recurrence or death) rate of 25% in the overall population. We further posit that the high-risk group will experience a hazard ratio (HR) of 2.0 relative to the low-risk group.

Applying the Freedman formula for survival comparisons:^[16]^

$$N_{\text{events }}=\frac{{\left(Z_{1-\frac{\alpha }{2}}+Z_{1-\beta }\right)}^{2}}{(\ln HR{)}^{2}}=\frac{(1.96+0.84{)}^{2}}{(\ln2{)}^{2}}\approx 43\text{ events }$$

Assuming a 25% event rate, at least 172 patients are needed to observe the required number of DFS events.

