In our preliminary retrospective investigation of 81 patients with stage I NSCLC (Chinese PKUPH cohort, named CHN-P), we observed that there are strong ancestry disparities in lung cancer and Asian NSCLCs exhibit diverse genomic features. Regrettably, only a small number of patients, all of whom were at stage I, and the multi-region sampling methods were not consistent.^[12]^ To deepen our understanding of intratumoral heterogeneity in Chinese lung cancer patients, we expanded our study to include patients with stage I-IIIA NSCLC and implemented a standardized multi-region sampling process. This approach not only allowed us to explore the molecular signatures and clonal evolution inside tumors but also enabled us to investigate the immune microenvironment in the marginal zone and normal lung tissue. By uncovering the evolutionary molecular mechanisms and changes in the immune microenvironment from normal to aggressive borderline to tumor, we aim to provide valuable insights for clinical diagnosis and treatment strategies of lung cancer. With the prevalence of neoadjuvant therapy and its limited clinical benefits, there is a growing interest in identifying biomarkers and immune characteristics that are related to therapeutic efficacy. Hu *et al*. mapped tumor microenvironment changes during neoadjuvant immunotherapy by utilizing single-cell sequencing on tumor and peripheral blood samples and identified FCRL4+FCRL5^+^ B cells, CD 16^+^CX3CR1^+^ monocytes, and plasma estrogen changes as novel biomarkers.^[13]^ Xia *et al*. found a positive correlation between TYROBP expression and favorable responses to neoadjuvant camrelizumab, which was associated with increased infiltration of CD8^+^ T cells and enhanced effector responses of natural killercells.^[14]^ However, there have been no studies employing multi-region sampling cohorts for multi-omics research to explore the association of tumor heterogeneity with neoadjuvant efficacy and long-term survival. This study addresses this gap by innovatively collecting multi-region samples post-neoadjuvant therapy to investigate spatial regression patterns of tumors and changes in intratumoral heterogeneity. Furthermore, we have integrated various advanced spatial omics technologies to gain a more comprehensive understanding of the molecular landscape under neoadjuvant therapy.

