##### Consideration for machine learning modeling

The novel lung cancer recurrence prediction model will be constructed based on machine-learning algorithms (section 5.2). For the model development, we adopt a ratio of 6:2:2 for the training, validation, and test sets. This division ratio is based on the consideration that 60% training provides adequate data for model fitting and feature selection, while 20% validation allows unbiased hyperparameter tuning, and 20% test ensures a fully held-out assessment to guard against overfitting. This ratio balances model complexity and evaluation rigor, as recommended for medium-sized cohorts.^[21, 22, 23]^ When 173 patients are recruited for statistical power in the training set, a total of 289 cases are required.

In summary, to address the above three dimensions of statistical consideration and the disruption caused by loss to follow-up, we plan to enroll 300 patients in the first phase. This provides sufficient power for survival analysis while also accommodating downstream modeling requirements.

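### The 25% two-year DFS event rate is credited to an all-stage-I cohort, and the claim of sufficient survival power at 300 patients fails over the lower part of the plan's own event-rate range

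*Protocol article*

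**What the plan says.** The survival calculation (Consideration for survival analysis) compares two-year DFS between high-risk and low-risk groups "using a two-sided log-rank test at α = 0.05 and 80% power (1-β = 0.80"). It posits that "the high-risk group will experience a hazard ratio (HR) of 2.0 relative to the low-risk group". For the event rate it writes "Based on our preliminary data (CHN-P cohort"), and then "we assume a 2-year DFS event (recurrence or death) rate of 25% in the overall population". It arrives at 43 events and 172 patients.

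The Introduction describes the source cohort: "In our preliminary retrospective investigation of 81 patients with stage I NSCLC (Chinese PKUPH cohort, named CHN-P"). It gives as a limitation that there were "only a small number of patients, all of whom were at stage I, and the multi-region sampling methods were not consistent".

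The trial population is wider. The inclusion criteria admit operable stage I to IIIA disease. Study design and highlights splits the cohort into a naïve and a neoadjuvant subcohort. Patient management says that stage II to IIIA is the group generally considered for neoadjuvant treatment.

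Other event rates appear elsewhere:
- The opening of Sample size calculation anticipates that "the proportion of recurrence events by the end of the follow-up period will range from 15% to 30" per cent.
- The recurrence-prediction validation section fixes two-year recurrence at 20%, although the legend under its formula says 0.25.
- The machine-learning section expects 80 events in 300 patients, or 26.7%.

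On the choice of 300 patients, the article concludes: "This provides sufficient power for survival analysis while also accommodating downstream modeling requirements".

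**The concern.** In a log-rank design the number of events sets the information, and the event rate turns patients into events. Here that input is said to describe the overall population but is credited to a cohort with no stage II or IIIA patients. The article itself names this as the cohort's shortcoming. No adjustment for stage mix or for neoadjuvant treatment is described.

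The power statement for 300 patients carries no condition, although the article expects a twofold range of recurrence rates. Two-year DFS is one of the primary endpoints. If the realised rate lies in the lower part of that range, the first-phase comparison has less than the 80% power that the calculation sets out to provide, and the text gives the reader no sign of it.

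**Working it through.** **Source against population.** CHN-P: 81 patients, retrospective, all stage I. CLEVER: stage I to IIIA, with a neoadjuvant subcohort. A stage-I-only cohort holds no observations on the stage II to IIIA patients who form part of the trial's overall population.

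**The plan's own figure.** The printed formula gives (1.96 + 0.84)² / (ln 2)² = 7.84 / 0.4805 = 16.3 events, not 43. The next step, 43 / 0.25 = 172, does reproduce. With the stated inputs and equal groups, the standard formulas give:
- Schoenfeld: 4 × (1.96 + 0.84)² / (ln 2)² = 65.3, so 66 events.
- Freedman: (1.96 + 0.84)² × [(2 + 1)/(2 − 1)]² = 7.84 × 9 = 70.6, so 71 events.

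With 43 events, power would be about 62% (Schoenfeld) or 59% (Freedman). This matters here because the wrong count hides the sensitivity to the event rate. Against 43 events, 300 patients at 15% (45 events) look adequate.

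**Power at 300 patients.** Inputs: HR 2.0 and two-sided 0.05, both from the survival section; D = 300 × rate, taking every patient as followed for two years. The group split is not stated. I assume 1:1, the most favourable case, and show 1:3 as a contrast.
- Schoenfeld: Φ(√(D·p(1−p)) × ln 2 − 1.96), with p the share of patients in one group; p = 0.5 for 1:1.
- Freedman, 1:1: Φ(√D / 3 − 1.96).

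Example at 25%: D = 75; √(75/4) × 0.693 − 1.96 = 1.04; Φ(1.04) = 0.85.

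| Rate | Where it stands in the article | Events | Schoenfeld 1:1 | Freedman 1:1 | Schoenfeld 1:3 |
|---|---|---|---|---|---|
| 15% | lower end of anticipated recurrence | 45 | 64% | 61% | 52% |
| 20% | recurrence-prediction validation | 60 | 77% | 73% | 64% |
| 25% | survival calculation | 75 | 85% | 82% | 74% |
| 26.7% | machine-learning section | 80 | 87% | 85% | 77% |
| 30% | upper end of anticipated recurrence | 90 | 91% | 89% | 81% |

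**Break-even.** For 80% power with equal groups, the event rate must reach 66/300 = 22% (Schoenfeld) or 71/300 = 23.7% (Freedman).

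**Loss to follow-up.** Missing data handling sets a 10% maximum. If those patients contributed nothing, leaving 270, Schoenfeld 1:1 power would be 60%, 72%, 81%, 84% and 88% in the order of the table. This is a lower bound, since a log-rank test uses follow-up up to censoring.

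**The case against.** A reader might infer that the stage I source makes 25% too optimistic and so causes the loss of power. The documents do not support that. Adding stage II to IIIA patients would be expected to raise the event rate, which gives more events and more power. If 25% is a stage I rate, it is more likely too low than too high for this cohort. This objection stands, and it limits the point to an unsupported input.

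A reader might also say that power is adequate only if 25% is exactly right. It is not so fragile: with equal groups, any rate of about 22% or more suffices, and the article's own 26.7% gives 87%.

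Nor do the rates flatly contradict one another. The 15–30% range and the 20% figure count recurrence, whereas the 25% counts recurrence or death. A DFS rate of 25% can sit beside 20% recurrence, and it lies inside the range. The 64% and 77% figures therefore treat recurrence rates as if they were DFS rates and may be somewhat pessimistic.

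The strongest remaining objection is that the shortfall appears only once the 43-event requirement is corrected. That is true, but correcting the count does not mend the rate: the answer at 300 patients would still rest on a 25% whose stated source covers only part of the population.

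Finally, timing the analysis by events would be a design preference. A test after two years of follow-up is legitimate for a two-year endpoint, and its timing may be left to a document not shown.

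**Conclusion.** The point holds as a limited one. The stated source of the 25% does not describe the population to which the rate is applied. That makes the input unsupported; it does not show an overestimate. The unqualified power claim for 300 patients is not true throughout the plan's own range. With HR 2.0, two-sided 0.05 and equal groups, power is about 64% at 15% and 77% at 20%. It reaches 85% at 25%, 87% at 26.7% and 91% at 30%, with the crossing at about 22%.

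These figures rest on the Schoenfeld approximation, complete two-year follow-up and an assumed 1:1 split. They also use the plan's recurrence rates as stand-ins for DFS rates, which may understate power somewhat. An unequal split works the other way: at 25%, power is 74% with 1:3. What rate CHN-P actually showed cannot be seen from the article.

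**What to change.** Three changes to the sample-size text:

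1. In Consideration for survival analysis, either label the CHN-P figure as a stage I rate or derive the overall DFS rate from stage-specific rates and the expected stage mix, saying how the neoadjuvant subcohort is treated.
2. In the same section, replace 43 with the event requirement that the stated inputs give: about 66 by Schoenfeld or 71 by Freedman with equal groups. Name the formula used and the assumed high-risk to low-risk split.
3. In the summary that follows Consideration for machine learning modeling, replace the general statement of sufficient power with the power at 300 patients across event rates of 15% to 30%. State the split, and say whether the rates are recurrence or DFS.

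The cost is a few sentences and one small table. Stage-specific rates have to be found and cited if the overall rate is rebuilt. The changes do not in themselves require a different enrolment target.

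### The 43 DFS events and 172 patients given for 80% power at HR 2.0 are wrong: the printed formula equals 16, the standard formulas with equal groups give 66 to 71 events, and 43 events give about 60% power

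*Protocol article*

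**What the plan says.** In the protocol article, the section *Consideration for survival analysis* sets out to "compare 2-year DFS between predefined high-risk and low-risk groups" with a two-sided log-rank test at 5% and 80% power. Two further assumptions are given: "we assume a 2-year DFS event (recurrence or death) rate of 25% in the overall population", and that "the high-risk group will experience a hazard ratio (HR) of 2.0 relative to the low-risk group". The calculation is introduced by "Applying the Freedman formula for survival comparisons". The expression that follows is the squared sum of the two normal quantiles divided by (ln HR)², with 1.96, 0.84 and ln 2 filled in and a result of about 43 events. The section then concludes: "Assuming a 25% event rate, at least 172 patients are needed to observe the required number of DFS events".

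The next-but-one section, *Consideration for machine learning modeling*, reaches 289 patients by a different route and then states that "we plan to enroll 300 patients in the first phase". It adds: "This provides sufficient power for survival analysis while also accommodating downstream modeling requirements". The share of patients expected in the high-risk group is not given.

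**The concern.** Every term of the calculation is printed, and the terms do not produce the printed answer. The formula is also not the one named. Either fault alone would need correcting; together they leave 43 events without a basis.

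The error runs in the unsafe direction. Two-year DFS is a primary endpoint (*Study design and highlights*), and this is the article's only power calculation for it. A reader who compares 172 with 300 sees 128 patients to spare. If the true need is 264 to 284, the margin is 36 or 16 patients before any loss. A later phase or another group that reused 43 events as its target would have about 60% power while claiming 80%.

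**Working it through.** **Inputs.** From *Consideration for survival analysis*: two-sided α = 0.05 (z = 1.96), power 80% (z = 0.84), HR = 2.0, overall two-year event rate 25%. From *Consideration for machine learning modeling*: 300 patients. From *Missing data handling*: maximum acceptable loss 10%. The risk split is not stated; equal groups are assumed first and then varied.

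**1. The plan's own line.** (1.96 + 0.84)² = 7.84 and (ln 2)² = 0.4805, so 7.84 / 0.4805 = **16.3**, not 43. Only the last step reproduces: 43 / 0.25 = 172.

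**2. Schoenfeld.** Events = 7.84 / [p(1−p)(ln HR)²], where p is the share in one group. With p = 0.5: 4 × 16.3 = 65.3, so **66 events** and 66 / 0.25 = **264 patients**.

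**3. Freedman, the formula named.** With equal groups, events = 7.84 × [(HR+1)/(HR−1)]² = 7.84 × 9 = 70.6, so **71 events** and 71 / 0.25 = **284 patients**.

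**4. Can any split give 43?**
- Schoenfeld would need p(1−p) = 16.3 / 43 = 0.38, and the maximum is 0.25.
- Freedman's general form replaces 9 by (1 + 2k)²/k, where k is the ratio of high-risk to low-risk patients. Its minimum is 8, at k = 0.5 (one third high-risk): 7.84 × 8 = 62.7, so 63 events.
- One-sided testing gives 52 (Schoenfeld) or 56 (Freedman), and the text says two-sided.

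**5. Power with 43 events at HR 2.0.**
- Schoenfeld, equal groups: Φ(√(43/4) × 0.693 − 1.96) = Φ(0.31) = **62%**.
- Freedman, equal groups: Φ(√43/3 − 1.96) = Φ(0.23) = **59%**.
- Freedman at its most favourable split: Φ(√(43/8) − 1.96) = Φ(0.36) = 64%.
- With equal groups, 43 events reach 80% power only at HR ≈ 2.35 (Schoenfeld: exp(2 × 2.8/√43)) or ≈ 2.49 (Freedman).

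**6. What 300 patients give at HR 2.0, equal groups.**

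| Scenario | Events | Schoenfeld | Freedman |
|---|---|---|---|
| 26.7% event rate (*Machine learning model development and validation*) | 80 | 87% | 85% |
| 25% event rate | 75 | 85% | 82% |
| 25%, with 10% of events lost | 67.5 | 81% | 78% |
| 20% event rate (*Consideration for recurrence prediction validation*) | 60 | 77% | 73% |
| 15%, lower end in *Sample size calculation* | 45 | 64% | 61% |

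Inflating the sample size for 10% loss gives 264 / 0.9 = 294 patients (Schoenfeld) or 284 / 0.9 = 316 (Freedman).

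**7. Sensitivity to the split, 75 events, 30:70.** Schoenfeld does not distinguish which group is smaller: 16.3 / 0.21 = 77.7, so 78 events are needed and power is 79%. Freedman does distinguish:
- 30% high-risk: k = 3/7, factor 8.05, Φ(√(75/8.05) − 1.96) = 86%.
- 70% high-risk: k = 7/3, factor 13.8, Φ(√(75/13.8) − 1.96) = 65%.

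**The case against.** The arithmetic error is hard to dispute, and text extraction does not explain it: putting back a lost factor of 4 gives 65, not 43. The serious objections concern what follows from it.

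- **Enrolment does not rest on 172.** The 300 comes from the 289 of the modelling section. At the stated 25% rate with equal groups, 300 patients exceed 80% power by either formula. This stands: the sufficiency statement is conditional rather than false.
- **The unfavourable cases may be too severe.** The 10% loss is a ceiling, and removing 10% of events assumes that lost patients contribute none. The article elsewhere expects 80 events. An unequal split need not hurt either: by Freedman's form, a high-risk minority of about a third does slightly better than equal groups. All of this stands. On the other side, the article's own lower event rates and a low-risk minority both bring power below 80%.
- **43 may come from another hazard ratio.** Freedman's formula at HR 2.5 gives 7.84 × (3.5/1.5)² = 42.7, hence 43 events and 172 patients. That is a possible origin and cannot be confirmed. It does not rescue the text, which states HR 2.0 in words and uses ln 2 in the formula. It does mean the authors should confirm the intended hazard ratio before choosing which figure to change.

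**Conclusion.** The concern holds. The printed expression equals 16.3, it is not Freedman's formula, and 43 events cannot be obtained at HR 2.0 with two-sided 5% α and 80% power under any split of patients. With equal groups the requirement is 66 events (264 patients) by Schoenfeld or 71 events (284 patients) by Freedman, so 172 is 35% to 39% too low. Forty-three events give 62% or 59% power.

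The practical damage is limited because 300 patients are planned. Under the 25% rate and equal groups, power is 85% or 82%; after 10% loss it is 81% or 78%. By the formula the protocol names, 300 therefore falls just short once the full loss allowance is used. The claim of sufficient power depends on an event rate near 25% and on a risk split that the article does not state. The patient numbers here take the 25% rate as given. The calculation covers DFS only, not the other primary endpoint, OS.

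**What to change.** 1. Confirm the intended hazard ratio. If it is 2.0, as written, remove 43 and 172.
2. Use one formula and name it correctly: Schoenfeld with the p(1−p) term, or Freedman with (HR+1)²/(HR−1)² in its equal-group form.
3. State the assumed share of patients in the high-risk group. With equal groups, report 66 events and 264 patients (Schoenfeld) or 71 events and 284 patients (Freedman) at a 25% event rate; otherwise recompute for the stated split.
4. Replace the general statement of sufficient power with the power that 300 patients give for that split, before and after 10% loss. With equal groups this is 85% and 81% (Schoenfeld) or 82% and 78% (Freedman). Add the result at a lower event rate, such as the 20% used elsewhere in the article.

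The cost is protocol wording. Enrolment can stay at 300, provided the protocol accepts that power after full loss is slightly under 80% by Freedman's formula (316 patients would be needed to meet it). The stated power becomes a little less favourable.

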##### Consideration for recurrence prediction validation

In this study, we aim to validate a machine-learning-based lung cancer recurrence prediction model with anticipated sensitivity of 90% ± 10% and specificity of 90% ± 10%. To calculate the necessary sample size for this diagnostic validation, we anchor our calculations to a fixed two-year recurrence (event) rate of 20%, based on retrospective study of recurrence after complete resection of early NSCLC.^[17, 18]^

Using Buderer’s formula for sensitivity and specificity sample size estimation:^[19, 20]^

$$N=\frac{Z^{2}\cdot p(1-p)}{d^{2}\cdot \text{ Prevalence }}=\frac{(1.96{)}^{2}\cdot 0.9\cdot 0.1}{0.1^{2}\cdot 0.2}\approx 173\text{ patients }$$

Here p is the anticipated sensitivity or specificity (0.90), d is the half-width of the 95% confidence interval (0.1), and Prevalence is the event prevalence (0.25). This calculation yields approximately 173 patients required to estimate sensitivity and specificity with ±10% precision at α = 0.05.

##### Consideration for machine learning modeling

The novel lung cancer recurrence prediction model will be constructed based on machine-learning algorithms (section 5.2). For the model development, we adopt a ratio of 6:2:2 for the training, validation, and test sets. This division ratio is based on the consideration that 60% training provides adequate data for model fitting and feature selection, while 20% validation allows unbiased hyperparameter tuning, and 20% test ensures a fully held-out assessment to guard against overfitting. This ratio balances model complexity and evaluation rigor, as recommended for medium-sized cohorts.^[21, 22, 23]^ When 173 patients are recruited for statistical power in the training set, a total of 289 cases are required.

In summary, to address the above three dimensions of statistical consideration and the disruption caused by loss to follow-up, we plan to enroll 300 patients in the first phase. This provides sufficient power for survival analysis while also accommodating downstream modeling requirements.

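### The 173 patients calculated for ±10-point validation precision are placed in the training set, so the 60-patient test set estimates sensitivity only to about ±17 points

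*Protocol article*

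**What the plan says.** Three places in the protocol article bear on this point.

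- **Consideration for recurrence prediction validation.** The aim is to validate a recurrence model with sensitivity and specificity both anticipated at 90%, each to within 10 points. Buderer's formula with a 20% two-year event rate gives "approximately 173 patients required to estimate sensitivity and specificity with ±10% precision".
- **Consideration for machine learning modeling.** First-phase patients are split 6:2:2. Training (60%) is for fitting and feature selection, validation (20%) for hyperparameter tuning, and test (20%) for the held-out assessment. The total is then derived: "When 173 patients are recruited for statistical power in the training set, a total of 289 cases are required". This is rounded up to 300 to cover loss to follow-up and is said to meet all three sample size considerations.
- **Machine learning model development and validation.** Tuning is confined to the training set. All candidate models are applied to the test set and the best is selected. Discrimination, calibration and clinical utility are assessed in the validation and test sets. External validation in two published cohorts and in later CLEVER phases follows, with no sample size or precision stated.

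**The concern.** A precision calculation of this kind gives the number of patients in whom sensitivity and specificity are estimated. It says nothing about how many are needed to fit a model. Assigning the 173 to training and dividing by 0.6 therefore has no statistical basis, and it leaves the set that does measure accuracy about one third of the size the article calculated for it.

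A reader would take the first phase to deliver sensitivity to ±10 points. It will not. Sensitivity is also the quantity that drives the 173, because recurrences are the minority class. With about a dozen recurrences in the test set, an observed sensitivity near 90% cannot exclude a model that misses more than a third of them.

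**Working it through.** **Inputs.** Anticipated sensitivity and specificity p = 0.90, half-width d = 0.10, Z = 1.96 and recurrence rate 0.20, all from the validation subsection. The 6:2:2 split and 300 patients come from the machine learning subsection. The recurrence range of 15% to 30% is under Sample size calculation. The 80 events in 300 (26.7%) are under Machine learning model development and validation. The maximum 10% loss is under Missing data handling.

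**1. Reproduce the article's figures.**
- N = Z² p(1−p) / (d² × prevalence) = 1.96² × 0.09 / (0.01 × 0.20) = 172.9, so 173. Reproduced.
- 173 / 0.6 = 288.3, so 289. Reproduced.
- The legend under the formula gives prevalence as 0.25, which would yield 138.3, so 139. The 173 rests on 0.20.

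**2. What the 173 represents.** The number of recurrences required is 1.96² × 0.09 / 0.01 = 34.6, about 35. This is the count needed in the set where sensitivity is estimated.

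**3. Precision in the test set.** Test set = 0.2 × 300 = 60. Half-width for sensitivity = 1.96 × √(0.09 / events).

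| Recurrence rate | Events in 60 | Sensitivity, test set | Events in 120 | Sensitivity, validation + test |
|---|---|---|---|---|
| 15% | 9 | ±19.6 | 18 | ±13.9 |
| 20% | 12 | ±17.0 | 24 | ±12.0 |
| 25% | 15 | ±15.2 | 30 | ±10.7 |
| 26.7% | 16 | ±14.7 | 32 | ±10.4 |
| 30% | 18 | ±13.9 | 36 | ±9.8 |

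At 20%, the specificity half-width in the test set is 1.96 × √(0.09 / 48) = ±8.5 points. It stays below ±10 over the whole 15% to 30% range.

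**4. Loss to follow-up.** With 10% loss the test set is 0.2 × 270 = 54. At 20% this gives 10.8 events and ±17.9 points.

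**5. Exact interval.** The normal approximation is rough with 12 events. If 11 of 12 recurrences are detected, the Clopper-Pearson 95% interval is 62% to 99.8%, so the exact calculation does not improve the picture.

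**6. Total needed if the 173 sit in the test set.** 173 / 0.2 = 865, or 865 / 0.9 = 961.1, so 962, allowing for 10% loss.

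**The case against.** The strongest reply is that 60 is not the only possible evaluation set. The model development section reports performance in both the validation and test sets and confines all tuning to training, so on that text the two could be pooled. Pooling gives ±12.0 points at 20%, ±10.4 at the article's own 26.7%, and ±9.8 at 30%. It stands that the shortfall is smaller on this reading. But the target is still missed at the rate the calculation uses and is met only at the top of the anticipated range. The sample size section also gives the validation set to tuning, which contradicts the later text and would make pooling unsafe.

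Second, ten-fold cross-validation within 180 training patients (36 events at 20%) has a nominal half-width of 1.96 × √(0.09 / 36) = ±9.8, so 173 in training might reflect cross-validated precision. The article does not give that rationale, and the same folds tune the hyperparameters, so the resulting accuracy would be optimistic.

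Third, ±17 is one point in a range, specificity meets the target, the model belongs to the secondary aim, and external validation will follow. All of this is fair, and it limits the consequences. It does not rescue the claim, because no size or precision is attached to the external validation and the 173 is presented as sizing the first phase.

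Lastly, the performance measures listed for the validation and test sets do not name sensitivity. That leaves the ±10-point commitment with no identified analysis behind it, which adds to the problem.

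**Conclusion.** The concern holds. The 173 is computed correctly from the stated inputs but assigned to the wrong set, and the ±10-point precision for sensitivity is not delivered by the first phase. On the article's 20% rate the test set gives ±17.0 points, and on its 15% to 30% range about ±20 to ±14. These figures assume a true sensitivity of 90%, a proportional split of 300 and no loss to follow-up; the accepted 10% loss widens ±17.0 to ±17.9. Specificity is not affected.

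The test-set estimate is also not strictly held out, because the final algorithm is chosen by comparing all candidates on that set. The interval widths above do not capture the resulting optimism. The 0.20 versus 0.25 mismatch is a separate slip and does not help: at 0.25 the requirement is 139, still more than twice 60.

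**What to change.** 1. Delete the step that places 173 in the training set and derives 289 from it.
2. State the precision the first phase gives: in a 60-patient test set, about ±17 points for sensitivity and ±8.5 for specificity at 20% recurrence, with the range for 15% to 30%. Report exact intervals.
3. Attach the ±10-point target to the later CLEVER phase already named for validation, as at least 173 evaluable patients. Adding a minimum of 35 recurrences would protect the target if the event rate is lower than 20%. Settle the 0.20 versus 0.25 prevalence first.
4. Reconcile the two statements on whether the validation set is used for tuning, and choose the final algorithm without using the test set.
5. Optionally, make nested cross-validated or bootstrap-corrected accuracy over all 300 the main internal estimate. Its nominal half-width is 1.96 × √(0.09 / 60) = ±7.6 points, or ±8.0 with 54 events after 10% loss. This is nominal only: it treats resampled predictions as independent, and it would replace the single split as the main assessment.

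The cost is wording, with no additional first-phase patients. First-phase precision will look less favourable on paper. Because 289 is the only calculation leading to 300 (the other two considerations print 172 and 173), the article also needs a new reason for 300, for example the number of events required for model development or feasibility stated as such.
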